The OptiBreech 1 opened in January 2021, with 10 sites gradually joining the study throughout 2021 due to delays with R&D approvals affected by the COVID-19 pandemic (https://optibreech.uk/participating-sites/). This is a preliminary observational and qualitative feasibility study, aiming to determine whether there is a demand for vaginal breech birth, whether it is possible to implement the OptiBreech model of care, and how acceptable the OptiBreech model is to women and staff. As of 9 September 2021, a total of 27 women requesting a vaginal breech birth have been recruited to the study across 4 sites. A brief summary table is presented below, comparing our returned results so far, alongside the largest reported study of ECV outcomes in the UK.^40^

Table 2: Results of OptiBreech 1

*OptiBreech 1* – conducted in the hospitals participating in this randomisation study (to 7/9/21)

| **Outcome** | **OptiBreech 1**  *planned vaginal breech births following or without ECV attempt* | **Melo et al 2019 ECV study**  *gold standard UK ECV pathway* |
| --- | --- | --- |
| Total vaginal births | 48% (13/27) | 43.6% (1141/2614) |
| Spontaneous vaginal birth | 44% (12/27) | 33.1% (866/2614) |
| Instrumental birth  *(forceps or suction cup)* | 4% (1/27) | 10.5% (275/2614) |
| Pre-labour caesarean birth | 19% (5/27) | 36.6% (957/2614) |
| In-labour caesarean birth | 33% (9/27) | 18.5% (484/2614) |
| Baby turned head-down prior to labour following failed ECV | 4% (1/27) | 4% (57/1334) |
| Admission to NICU / SCBU* | 4% (1/27) | 3.6% (95/2614) |
| Stillbirth or neonatal death (within 28 days of birth) * | 0 | 0.19% (5/2614) |
| Someone present who had completed physiological breech birth training | 83% (10/12) | *Not reported* |
| Someone present who met all proficiency criteria | 75% (9/12) | *Not reported* |
| Less than 5 minutes elapsed between the birth of the pelvis and the birth of the head | 92% (11/12) | *Not reported* |
| Maternal birth position | Upright – 83% (10/12)  Supine (back) – 17% (2/12) | *Not reported* |

* The OptiBreech 1 study has not collected enough data to make a comparison on these outcomes, but we would expect results to be similar, based on the RCOG Guidance described below.

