Although it is too early to conclude anything from these results, a few observations can be made. Firstly, where a genuine specialist midwife is in operation and attending most/all of the vaginal breech births, as is/was the case in two of the sites, there appears to be a significant demand for this service. These two Trusts, comprising a total of three hospitals, have been responsible for 21/27 of the women recruited in the OptiBreech 1 study. They are the only two sites to meet the inclusion criteria for OptiBreech Care. There has been 100% proficient attendance at these sites and no neonatal admissions.

In contrast, attempts to set up a multi-disciplinary team at other sites have been largely unsuccessful or are progressing slowly. This may be because the implementation approach used is not adequate/feasible or because the demands of dealing with the pandemic have hampered the ability to develop specialist skills within a service where they are not already operational. For example, several sites have indicated face-to-face training is needed, but this has been very challenging to arrange due to social distancing measures in place and persistent staff shortages. All adverse outcomes and lack of attendance of proficient OptiBreech team members have been in sites not currently included in this randomisation pilot. We will continue to observe what is happening in these sites to gain insight over a longer period of time, but no site will be able to randomise women in this study until the site eligibility criteria have been met.

Finally, our team has completed a review of outcomes associated with effectiveness studies of breech birth at term.^54^ This included significant involvement of our PPI group, to ensure that women’s voices influenced our choice of outcome data points. The influence they have had on our work is described in the publication.

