# Participant Selection

## Sites

All NHS sites who are providing OptiBreech Care are eligible to contribute data to the cohort study.

Site requirements for participation in the pilot randomisation include:

1. Recruited a minimum of 5 women to OptiBreech 1 or the non-randomised cohort of OptiBreech mTC
2. Achieved at least 90% fidelity to the intervention (attendance of someone with training and/or proficiency, <5 minutes from pelvis to head and use of maternal movement and effort prior to hands-on assistance) for a minimum of 5 vaginal breech births
3. Able to present a plan for recruitment and randomisation for a minimum of 2 women per month who provide fully informed consent to taking part in the study, immediately following diagnosis of breech presentation by USS, prior to counselling for ECV/mode of birth
4. Able to ensure a member of the OptiBreech team is available to provide counselling for women randomised to ‘offer OptiBreech Care’
5. Able to include the Physiological Breech Birth Algorithm in annual mandatory training activities for all staff. This should cover: The recommended 7-5-3 minute time limit guidance; actions in response to delay in second stage, including delay on the perineum; physiological neonatal transition, including initiation of resuscitation where required with umbilical cord intact; effective communication; and maintaining a helicopter view
6. Identification of a Breech Specialist Midwife and/or Obstetrician with dedicated time to co-ordinate OptiBreech care and training, ability to deliver the physiological breech birth training package and commitment to participate in on-going professional development seminars provided by the research team throughout this trial.

Sites will be able to demonstrate adherence to these criteria during their participation in the OptiBreech 1 study.

We will initially include 2 Trusts, including 3 hospital sites, in the randomisation pilot. Approximately 4% of women have a breech pregnancy at term, and we can expect at least half of these to be eligible for randomisation. Feasibility testing as part of OptiBreech 1 indicated that we can anticipate half of these again, or 1% of all women, will consent to randomisation in this study. Sites will be expected to recruit a minimum of 10 participants willing to be randomised over a 6 month period.

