## 14.3 Interim analysis and data monitoring

### Green/Amber/Red Criteria for recommending a full RCT

As this is a pilot trial, there will be no interim analysis. Rather, the TSC review at the end of the pilot trial will serve as data monitoring, as part of the overall decision about whether to proceed with a substantive trial. All unexpected serious adverse events will be reported to the TSC, and the TSC will have the power to pause the trial to assess unblinded data if that appears necessary for ensuring participants’ safety, as well as the power to stop the trial if participants’ safety appears to be at risk.

The following will be used to determine the feasibility of comparing standard care versus OptiBreech care:

A = total number of women randomised to OptiBreech VBB care

B = number of women declining OptiBreech VBB care in favour of ECV or CS first

C = total number of women randomised to ECV / standard care

D = number of women declining ECV attempt in favour of VBB or CS first

E = number of women lost to follow-up

F = number of sites participating in OptiBreech 2

G = number of months to achieve 104 recruits

H = number of sites in OptiBreech 1 meeting requirements for participation

J = number of additional sites indicating interest in joining the trial

Total women required for randomisation: 2280 to compare the outcome of ‘neonatal admission’ using current evidence on incident rates

48 women / month for 48 months

Green for trial: ($\frac{\left( A-B \right)+\left( C-D \right)-E}{F(G)})*(F+H)$ > 48 women

Amber: ($\frac{\left( A-B \right)+\left( C-D \right)-E}{F(G)})*(F+H+J)$ > 48 women

Red: ($\frac{\left( A-B \right)+\left( C-D \right)-E}{F(G)})*(F+H+J)$ < 48 women

For example:

104 women (A+C) are recruited by 5 months (G = 5)

52 are randomised to OptiBreech care (A = 52) but 30 decline this in favour of ECV or CS (B = 30)

52 are randomised to ECV (C = 52) but 20 decline this in favour of CS or VBB (D = 20)

2 women are lost to follow-up (E = 2)

5 sites participated in OptiBreech 2 (F = 5)

10 more sites in OptiBreech 1 are meeting participating criteria (H = 10)

25 more sites not currently participating have expressed an interest (J = 25)

($\frac{\left( A-B \right)+\left( C-D \right)-E}{F(G)})*(F+H)$ = 31.2

($\frac{\left( A-B \right)+\left( C-D \right)-E}{F(G)})*(F+H+J)$ = 83.2

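### The Green/Amber/Red rule defines H so that it can include sites already in F, its example reads H as additional, and F×G equals site-months only if all sites open together

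*Protocol*

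**What the plan says.** The rule is in Protocol section 13, under Green/Amber/Red Criteria for recommending a full RCT. The monthly rate per site is [(A−B)+(C−D)−E]/(F×G). It is multiplied by F+H for Green and by F+H+J for Amber and Red, and compared with 48 women a month. F is the number of sites in the pilot, G the months taken to reach 104 recruits, and J the further sites that have expressed interest. For the remaining term, "H = number of sites in OptiBreech 1 meeting requirements for participation".

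The worked example takes F = 5, G = 5 and J = 25 and words the H input differently: "10 more sites in OptiBreech 1 are meeting participating criteria (H = 10". It obtains 31.2 and 83.2 and concludes Amber. The sentence after it says that success depends on how many sites can develop their service far enough to qualify.

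Three other places bear on the site counts:

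- Section 4, Feasibility Testing, describes OptiBreech 1 "with 10 sites gradually joining the study throughout 2021". Of two Trusts with three hospitals between them it says "They are the only two sites to meet the inclusion criteria for OptiBreech Care".
- Section 7, Sites: "We will initially include 2 Trusts, including 3 hospital sites, in the randomisation pilot". A site may qualify on its recruits to OptiBreech 1 or to the non-randomised cohort.
- Section 13, Sample size calculation, expects five sites over six months.

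**The concern.** The site multiplier largely decides the light, and its terms are not fixed unambiguously.

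First, nothing in the definition of H removes sites already in F. The pilot's first Trusts qualified through OptiBreech 1, so on the written definition they count in both terms. The example assumes the opposite. Two people applying the rule to the same pilot data could therefore report different projections.

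Second, G is calendar time for the whole pilot. F×G is the true exposure only if every site could randomise for all G months. A pilot that starts with three hospitals, expects five sites and bars any site from randomising until it qualifies is unlikely to meet that condition.

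Third, sites that have only expressed interest enter at the full rate of the selected pilot sites. The text attaches a condition to this, but the formula does not carry it.

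The Trial Steering Committee's recommendation on a substantive trial is to be informed by this rule, so an ambiguous multiplier matters even in a feasibility study.

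**Working it through.** **Inputs (worked example).** A = 52, B = 30, C = 52, D = 20, E = 2, F = 5, G = 5, H = 10, J = 25. Threshold 48 (2280/48 = 47.5, rounded up).

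**Reproducing the Protocol's figures.** Net count = (52−30) + (52−20) − 2 = 52. Rate = 52/(5×5) = 2.08 per site per month. Green quantity = 2.08 × 15 = 31.2. Amber quantity = 2.08 × 40 = 83.2. Both agree with the Protocol.

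**Overlap of F and H.** If the five pilot sites lie within OptiBreech 1 and that study has ten sites, there are ten distinct sites. This holds whether H = 10 contains F, or H is additional and equals 5.

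- Green quantity: 2.08 × 10 = 20.8, against 31.2 (31.2/20.8 = 1.5).
- Amber quantity: 2.08 × (10+25) = 72.8, against 83.2 (83.2/72.8 = 1.14).
- 72.8 exceeds 48, so the example remains Amber.

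**Can the overlap change a light?** Keep F = 5, G = 5, H = 10. As written, Green needs net/25 × 15 > 48, that is, a net count above 80. With ten distinct sites it needs net/25 × 10 > 48, a net count above 120, which 104 recruits cannot supply. With all five sites open for all five months, a net count of 81 to 104 would therefore be a false Green.

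**Exposure.** The Protocol gives no opening schedule, so what follows is assumed. On the planned six months, three sites open for six months and two for three months give 3×6 + 2×3 = 24 site-months, against F×G = 30. The rule's rate is then 24/30 = 0.80 of the true rate, 20% too low.

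For the example (G = 5), suppose three sites are open for all five months and the other two for m months each. Site-months are S = 15 + 2m, and Green with ten distinct sites needs a net count above 48 × S/10 = 4.8S:

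| m | S | rate (52/S) | ×15 | ×10 | net count needed for Green, ten sites |
|---|---|---|---|---|---|
| 5 | 25 | 2.08 | 31.2 | 20.8 | above 120 (impossible) |
| 3.5 | 22 | 2.36 | 35.5 | 23.6 | above 105.6 (impossible) |
| 2 | 19 | 2.74 | 41.1 | 27.4 | above 91.2 |
| 0 (limit) | 15 | 3.47 | 52.0 | 34.7 | above 72 |

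The written cut-off of 80 equals 4.8S at S = 16.7. Above that, the written rule is too easy to pass; below it, too hard. The two faults pull in opposite directions, and which one dominates depends on opening dates.

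**Interested sites.** At 2.08 per site, 48 a month needs 48/2.08 = 23.1 full-rate sites. The break-even share of the 25 J sites is (23.1−15)/25 = 32% with F+H = 15, or (23.1−10)/25 = 52% with ten distinct sites. Over assumed shares:

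| share of J at full rate | F+H = 15 | ten distinct sites |
|---|---|---|
| 100% | 83.2 | 72.8 |
| 75% | 70.2 | 59.8 |
| 50% | 57.2 | 46.8 |
| 25% | 44.2 | 33.8 |

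**The case against.** The best defence is that the example shows the intent. It calls the H sites further ones and the J sites not currently participating, so F, H and J are disjoint, and the missing exclusion is a slip of wording. The arithmetic is exact and the inputs are openly hypothetical. Sites may also qualify through the cohort, so F need not lie within OptiBreech 1. Much of this stands, and it is why the fault is a conflict between definition and example rather than a proven double count. It does not rescue the example's site numbers: all five pilot sites would have to have come by the cohort route, whereas the two Trusts already qualifying did so through OptiBreech 1.

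A reader might go further and say that projected recruitment is doubled on today's sites, with F and H being the same three hospitals (6 counted for 3). That follows only from the literal definition. On the example's reading H is 0 today and nothing is doubled.

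On J, it is fair to reply that Amber is meant as a conditional, best-case reading and that the text says so. It is also fair that the committee includes an independent statistician and holds the final decision, that acceptance and attrition are reported separately, and that no participant-level estimate is affected. These points limit the harm, but they do not settle what H means or how exposure is counted.

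**Conclusion.** The point holds in a limited form. The definition of H and the worked example contradict each other, and the example's 15 sites do not fit a pool of ten OptiBreech 1 sites unless the five pilot sites entered by the cohort route. If F lies within H and the pool stays at ten, the example overstates the Green quantity 1.5-fold and the Amber quantity 1.14-fold. Its Amber result stands. A false Green at net counts of 81 to 104 is possible with these site numbers if all sites are open throughout; staggered opening narrows that range and, in the extreme, reverses the error. The staggered schedules are assumptions, and the size of that effect is unknown until opening dates are recorded.

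A reader might also infer that the example turns Red once J is discounted. Taking 3 of 10 OptiBreech 1 sites as the conversion share gives 2.08 × (15+7.5) = 46.8, just under 48. The documents do not support that conclusion. The share mixes hospitals with sites, since the Protocol counts those three hospitals as two sites. It was taken while sites were still joining, when only four had recruited. It misses the break-even of 32% by about two points. Raising the rate for the assumed 20% exposure shortfall (2.08/0.80 = 2.60) moves the same figure to 58.5. What can be said is that the Amber result is sensitive to a conversion share that the rule does not state.

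**What to change.** Make four changes to the criteria before pilot data are reviewed:

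1. Define H as OptiBreech 1 sites that meet the requirements and are not already counted in F, and say whether a site is a Trust or a hospital.
2. Replace F×G by the sum, over pilot sites, of the months each was open to randomisation.
3. Redo the worked example with site numbers that fit the real pool.
4. Report the Amber quantity over a stated range of conversion shares for J, with the break-even share, so that the condition now given only in the text is visible in the result.

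The cost is two definitions, one example and a short table. The only extra data needed are each site's opening dates for randomisation, which can be logged as sites open. Recruitment, allocation and participant data collection are unaffected.

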### Monitoring, quality control and assurance

This feasibility study is being completed as part of an NIHR Advanced Fellowship. All statistical calculations will be done by the Fellow and Chief Investigator, [name], who will have access to statistical support within the research team. An independent statistician will be appointed to the TSC, and they will be provided with all original data.

Local R&D offices will ensure all PIs have current good clinical practice training in place before authorising the site to open.

# Ethical considerations

## COVID-19 precautions

This research is being initiated during a pandemic and associated public health social distancing measures to limit the spread of the virus. All hospital and government policies will be followed to maintain these precautions, for as long as they are in effect.

Wherever possible, we will seek to provide participant information and to take consent electronically, to minimise contact. Where patients have not provided an e-mail address to the NHS service providing their maternity care, or not given permission for it to be used in this way, we will provide a paper copy. Any PIS or consent form will be made available for download for all participants.

We will also record a video description of the study and explanation of the consent form, provided exactly as it would be in practice, to minimise face-to-face time required to take consent. We will also record a description of physiological breech birth and the informed decision-making content available from the current RCOG guideline, to minimise face-to-face contact time and ensure consistent information about potential risks and benefits is available to women in multiple formats. These will be available from the feasibility study website, https://optibreech.uk.

Theoretical training will also be provided on-line through a Learning Management System platform, so that completion and comprehension testing can be tracked. Face-to-face training will focus on hands-on manoeuvres and occur for limited amounts of time and limited participants, with protective precautions in place. Cascade training is already an integral part of the intervention, as it enables those responsible for delivering the intervention to consolidate their own skills,^68^ so the research team will have face-to-face contact with as few local team members as needed.

## Peer and Ethical Review

The study design was peer reviewed by an external expert panel and the NIHR selection panel as part of the process of gaining NIHR grant funding. Peer review and PPI work concerning specific aspects of the study has continued during the protocol-writing stage. The protocol was reviewed and approved by all members of the research team. The entire protocol was externally reviewed by an ethics specialist within the NIHR Research Design Service London, with a favourable opinion, and the Principal Investigators from sites most likely to qualify for randomisation readiness.

Additionally, there is potential for staff to feel the research team is judging and/or criticising their expertise or professionalism and the way they currently practice. Staff may also feel guilty if they have previously been involved with an adverse outcome that they now feel could have been prevented and may also need support. Care will be taken to reassure staff that the intention is to test an innovation that may potentially improve outcomes, rather than to take issue with care that has been delivered according to current standards. We will also seek to establish a ‘learning culture’ by encouraging reflection on every birth, including what could have been done better, so that staff feel safe to explore these issues without fearing they will be considered incompetent. Feedback from PIs and staff members in OptiBreech 1 so far indicates that the staff experience of participating in the research so far has been very positive. We have had positive feedback particularly from our reflective webinars, covering learning points arising in sites participating in OptiBreech 1. Our formal qualitative implementation evaluation is on-going.

## PPI & Ethics

The same potential exists within PPI work that recounting past experiences of difficult births may cause distress, and indeed this has happened throughout the project to date, so we have had to be very careful about our follow-up support arrangements. PPI members may disclose poor/negligent care that puts present women at risk of harm. Giving birth is a very personal yet very common experience, and similar sensitivities may also be raised within the research team. Therefore, PPI contributors, Trial Steering Committee members and Co-researchers are given clear guidance about their role and the importance of maintaining confidentiality. Information about how to alert the CI or RA that they require support is also provided, and the same procedures will be followed as for participants should either distress or concerns arise.

In response to PPI participants expressing the isolation they felt while planning their own breech births and a wish for more opportunities for peer support, an OptiBreech FaceBook group has been created, which is open only to participants and professionals involved in the project. The group is facilitated by a PPI lead who has previously completed training on listening skills and receives guidance from the research team. All women are given information about this opportunity at enrolment in the study.

The most significant issue identified through PPI work concerning the design of this research was around informed consent for randomisation. Service users were concerned about women being informed about a specialist team being available but being unable to access this if randomised to the control arm. In response, the design has been modified to a Trial Within Cohort (TWiC) model,^57^ which uses a patient-centred two-stage consent process, in which participants are only provided with information that is relevant to them.^73^ Feedback suggests this will help resolve this tension while preserving the scientific integrity of the investigation. The PPI group has reviewed the specific consent form we are proposing to use in this research, which was revised with their feedback and received a favourable opinion from those who reviewed it.

